**Methods:**

EFFORT-MIBC is a multicentric prospective phase II trial aiming to include 156 patients. Eligible patients are patients with histopathology-proven MIBC or ≥ T3 on conventional imaging treated with MIBC radical treatment, without extra-pelvic metastases on conventional imaging (thoracic CT and abdominopelvic CT/ magnetic resonance imaging (MRI)). All patients will undergo radical local therapy and if eligible neo-adjuvant chemotherapy. An ^18^F-FDG-PET-CT will be performed in addition to and at the timing of the conventional imaging. In case of presence of extra-pelvic metastasis on ^18^F-FDG-PET-CT, appropriate intensification of treatment with metastasis-directed therapy (MDT) (in case of ≤3 metastases) or systemic immunotherapy (> 3 metastases) will be provided. The primary outcome is the 2-year overall survival rate. Secondary endpoints are progression-free survival, distant metastasis-free survival, disease-specific survival and quality of life. Furthermore, the added diagnostic value of ^18^F-FDG-PET-CT compared to conventional imaging will be evaluated and biomarkers in tumor specimen, urine and blood will be correlated with primary and secondary endpoints.

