### Objectives

The primary endpoint is the 2-year overall survival (OS) rate defined as the percentage of patients alive at 2 years after diagnosis of MIBC. OS is calculated from time of diagnosis until death due to MIBC or other causes.

Secondary endpoints are progression-free survival (PFS, defined as time of diagnosis until progression: i.e. local (T2-T4 in case of of TMT)/locoregional recurrence or extra-pelvic metastases), distant metastasis-free survival (DMFS, defined as time of diagnosis until occurrence of distant metastasis on repeated imaging), disease-specific survival (DSS, defined as time of diagnosis until death due to MIBC) and quality of life (QOL) evaluated by the general EORTC QOL questionnaire QLQ-C30 (version 3) and the bladder cancer specific module QLQ-BLM30. The added diagnostic value of ^18^F-FDG-PET-CT compared to conventional imaging will be evaluated. If neo-adjuvant chemotherapy is administered, the treatment response will be evaluated on the repeated ^18^F-FDG-PET-CT. A biopsy specimen of the bladder, obtained after transurethral resection of the bladder (TURb) as well as urine and blood samples will be collected for validation of predictive biomarkers by evaluating the correlation between response to therapy and outcome (PFS, DMFS, DSS and OS) with in literature reported biomarkers determined on biopsy specimen of the bladder, obtained after TURb.

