### Evaluation and inclusion

Patients who were recently diagnosed with MIBC on TURb and who are considered for curative treatment, will be informed of this clinical study if eligible at the departments of urology, radiation oncology, medical oncology or at the multidisciplinary consultations as carried out in some participating centers. The decision to participate will be entirely voluntary. Eligible patients who decide not to participate will be offered standard of care treatment.

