### Intervention

#### Imaging

Conventional imaging, consisting of standard thoracic CT and abdominopelvic CT (or MRI), will be performed prior to the radical local therapy. In case of neo-adjuvant chemotherapy, conventional imaging will be performed prior to and after neo-adjuvant chemotherapy. After the second cycle of chemotherapy, MRI bladder will be performed to evaluate provisional therapy response. In addition to and at timing of the conventional imaging patients will receive an ^18^F-FDG-PET-CT. We aim to perform the ^18^F-FDG-PET-CT within 1 month of the thoracic CT and abdominopelvic CT (or MRI).

The ^18^F-FDG-PET-CT procedure is described in detail in an additional file (see Additional file 2).

Conventional imaging images will be evaluated by experienced radiologists in uro-oncology. ^18^F-FDG-PET-CT images will be reviewed and analyzed by a nuclear medicine physician and a radiologist experienced in reading PET-CT images. Evaluation of the ^18^F-FDG-PET-CT images will occur blinded to the conventional imaging or vice versa in case the ^18^F-FDG-PET-CT is performed first.

After ruling out presence of distant metastases on conventional imaging and evaluation of the ^18^F-FDG-PET-CT’s, patients will be allocated to the appropriate treatment arm:
Arm 1: ^18^F-FDG-PET-CT ➜ T1–4 N0–3 M0Arm 2: ^18^F-FDG-PET-CT ➜ T1–4 N0–3 M1 (≤3 metastases)Arm 3: ^18^F-FDG-PET-CT ➜ T1–4 N0–3 M1 (> 3 metastases)

If no neo-adjuvant chemotherapy is administered, group allocation is based on the findings of the single ^18^F-FDG-PET-CT. In case of neo-adjuvant chemotherapy, group allocation is based on ^18^F-FDG-PET-CT with the highest number of distant metastases. Thus, patients who show a decrease of the total number of metastases or a complete response on the second ^18^F-FDG-PET-CT, will be allocated based on the result of their first ^18^F-FDG-PET-CT.

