#### Treatment

All included patients will receive a standard of care approach which involves either RC with extended pelvic lymph node dissection (ePLND) or TMT consisting of a visible complete TURb and radiochemotherapy. Radiochemotherapy consists of moderately hypofractionated radiotherapy to a dose of 55 Gy in 20 fractions to the bladder, in combination with a radiosensitizer. In case of clinically node-positive disease, the pelvic nodal areas are included in the radiotherapy field. Decision of local therapy is at the discretion of the patient unless there is a contraindication for one treatment option. If the patient is eligible, neo-adjuvant chemotherapy will be administered.

^18^F-FDG-PET-CT information concerning the pelvic lymph nodes will be used to guide local treatment i.e. adapting the ePLND template or radiotherapy field, if feasible.

According to the risk-group allocation, treatment will be intensified by adding MDT or immunotherapy, in treatment arm 2 or 3, respectively. Patients will not be randomized. Both surgery and stereotactic body radiation therapy (SBRT) can be applied as MDT for oligometastases. The SBRT procedure is described in detail in an additional file (see Additional file 3). In treatment arm 3, systemic immunotherapy will be initiated in case of ^18^F-FDG-PET-CT detected polymetastatic disease. The systemic immunotherapy protocol can be adjusted following changes in guidelines and/or reimbursement criteria.

In case of diagnosis of metastases on the conventional imaging before local treatment is started, the patient is excluded from the trial and metastatic bladder cancer standard of care is initiated.

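### The Objectives promise validation of predictive biomarkers, but the design has no contrast that could show a marker predicts benefit from MDT or immunotherapy

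*Protocol article*

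**What the plan says.** The Objectives section of the protocol article says that "urine and blood samples will be collected for validation of predictive biomarkers by evaluating the correlation between response to therapy and outcome" and literature-reported biomarkers, where outcome means PFS, DMFS, DSS and OS. The abstract describes the same work more cautiously: biomarkers in tumour specimen, "urine and blood will be correlated with primary and secondary endpoints".

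The rest of the article fixes who receives what:

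- **Randomisation** (Treatment): "Patients will not be randomized".
- **Intensification** (Treatment): "According to the risk-group allocation, treatment will be intensified by adding MDT or immunotherapy, in treatment arm 2 or 3, respectively". The arms are defined under Imaging as M0, up to 3 metastases, and more than 3 metastases on PET-CT.
- **Two scans** (Imaging): after neo-adjuvant chemotherapy, "group allocation is based on ^18^F-FDG-PET-CT with the highest number of distant metastases", so a patient whose metastases regress stays in the arm set by the first scan.
- **Refusal** (Inclusion and Exclusion criteria): willingness to undergo MDT or immunotherapy is required, and refusal excludes the patient.
- **Non-participants** (Evaluation and inclusion): "Eligible patients who decide not to participate will be offered standard of care treatment". They are not described as a comparison group.
- **Local therapy** (Treatment): "Decision of local therapy is at the discretion of the patient unless there is a contraindication for one treatment option".
- **Chemotherapy** (Treatment): "If the patient is eligible, neo-adjuvant chemotherapy will be administered". The Objectives add that response will be read on the repeated PET-CT.
- **Biomarker analysis** (Subsequent analyses): Mann-Whitney U, Wilcoxon signed-rank and Spearman correlation. No marker-by-treatment comparison is named.

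**The concern.** A prognostic marker separates patients with better and worse outcomes under a given treatment. A predictive marker separates patients who gain more from a treatment from those who gain less. The second is a statement about an interaction and needs the treatment effect at each marker level. The Objectives use the stronger term, together with the word validation, but the method they give is correlation.

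What is at stake is what may be concluded. An association between a marker and survival in arms 2 and 3 could be read as grounds for choosing patients for MDT or immunotherapy, although the data would be equally compatible with a marker that says nothing about benefit from either. Separately, a marker linked to metastatic burden would show an association with outcome if the arms were analysed together, simply because burden defines the arms.

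**Working it through.** **Figures in the plan.** The plan gives no figure for the biomarker objective. Its only sample size concerns 2-year OS in arms 2 + 3, and it reproduces. Testing 63% against 38% with an exact binomial test at 0.025 per side, n = 35 rejects at 20 or more survivors, with attained alpha 0.0167 and power 81.5%. Then 35/0.9 = 38.9, rounded up to 39, and 39/0.25 = 156. It is used below only for the expected split: 39 PET-positive and 156 − 39 = 117 PET-negative patients.

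**Step 1: what can be estimated.** For PET stratum s, marker m (0 or 1) and intensification T (0 or 1), write

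logit P(alive at 2 years) = α_s + β_s·m + T·(γ_s + δ_s·m),

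where β_s is the prognostic effect of the marker and δ_s is its predictive effect. By design T = 0 for everyone in arm 1 and T = 1 for everyone in arms 2 and 3.

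- In arm 1 the marker slope is β_1.
- In arm 2 it is β_2 + δ_2, and in arm 3 it is β_3 + δ_3. Only the sums can be estimated.
- Comparing arm 2 with arm 1 gives β_2 + δ_2 − β_1. This equals δ_2 only if β_2 = β_1, that is, if the marker has the same prognostic effect in M0 and oligometastatic disease. These data cannot check that. The same holds for arm 3.

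**Step 2: an illustration with assumed rates.** Let all patients be intensified, with equal marker groups and 2-year OS of 75% (marker-positive) and 51% (marker-negative). The mean is (75 + 51)/2 = 63%, the plan's assumption for arms 2 + 3.

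Odds ratio = (0.75/0.25) / (0.51/0.49) = 3.00/1.04 = 2.88.

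| Truth | OR if not intensified | OR if intensified | Interaction ratio |
|---|---|---|---|
| Purely prognostic | 2.88 | 2.88 | 1.0 |
| Purely predictive | 1.0 | 2.88 | 2.88 |

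The trial observes only the third column, which is the same in both rows.

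**Step 3: the other treatments.** Chemotherapy and local therapy do vary within a PET stratum, so the obstacle in Step 1 does not apply to them. But chemotherapy follows eligibility, and cystectomy or trimodality therapy follows patient choice or contraindication. Both may be related to prognosis, so a marker-by-treatment comparison would be confounded.

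**Step 4: the link with stage.** Suppose a marker relates to survival only through PET status, that 1/4 of patients are PET-positive (the plan's figure), and that PET groups differ by g points in 2-year OS. The pooled marker difference is then g × [P(PET+ | marker+) − P(PET+ | marker−)]. With assumed marker frequencies:

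| Marker in PET+ / PET− | P(PET+ given marker+) | P(PET+ given marker−) | Share of g inherited |
|---|---|---|---|
| 40% / 30% | 0.100/0.325 = 31% | 0.150/0.675 = 22% | 9% |
| 60% / 30% | 0.150/0.375 = 40% | 0.100/0.625 = 16% | 24% |
| 80% / 20% | 0.200/0.350 = 57% | 0.050/0.650 = 8% | 49% |

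The plan gives no survival assumption for arm 1, so g is left open. Stratifying by arm removes the component that comes from PET status in this example. It does not separate β from δ.

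**The case against.** The best defence is that the dispute is about a word. The Objectives say how validation will be done, by correlation, and the abstract says no more than that. Nothing in the article announces an interaction test or marker-based choice of treatment, and the lack of randomisation is stated openly. The objective is not primary and affects neither the sample size, nor arm allocation, nor patient care. All of this is true, and it keeps the point small. It does not remove it: the claim is made in the Objectives and the design cannot meet it.

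Four stronger readings are tempting but not supported:

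- **That PET determines all treatment, so that only prognosis can be studied.** PET determines MDT and immunotherapy. For chemotherapy there is a direct response readout, and asking whether a marker is associated with response among recipients is legitimate. It does not validate differential benefit without a comparator.
- **That a 35-point survival gap measures the problem.** The Background reports that difference as the result of a cited earlier study, not as an expectation for this cohort. Effective intensification would narrow it.
- **That the plan pools the arms.** The article does not say in which population the correlations are computed, and such detail may stand in the full protocol or analysis plan. The silence is not itself a fault.
- **That a burden-tracking marker will be reported as validated.** This is a forecast about reporting, and no passage bears it out.

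**Conclusion.** The point holds in a limited form. The stated aim of validating predictive biomarkers asks for something the design does not contain: by design, there is no information on a marker-by-intensification interaction within any PET stratum. This follows from the allocation rule, the absence of randomisation and the exclusion of refusers, and no later analysis plan can change it. It assumes that patients are treated as allocated. PET-positive patients who in practice miss intensification would be few and selected, and would not form a valid comparator.

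There is no single numerical size. The odds ratio of 2.88 shows that the two explanations cannot be told apart under assumed rates. The inherited shares of 9% to 49% show how far a stage-linked marker could reflect stage if the arms were pooled, again under assumed frequencies. A reader might infer that the biomarker work is worthless or that the primary analysis is affected. Neither follows. Association with outcome, and with response among chemotherapy recipients, can be studied, and the 2-year OS analysis is untouched. The change is worth making because it costs little and limits what may be concluded.

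**What to change.** 1. In the Objectives, replace the aim of validating predictive biomarkers with evaluating the association of literature-reported biomarkers with outcome, and with response to neo-adjuvant chemotherapy in those who receive it. This matches the abstract.
2. State that no claim of predicting benefit from MDT or immunotherapy will be made from these data.
3. State that outcome associations will be stratified by PET arm, so that a marker linked to stage is not credited with the survival difference between stages. Recommend this as a safeguard, not as a correction of a pooled analysis.

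The cost is a wording change and one stratification term, with no effect on sample size, data collection or treatment. The downside is a more modest claim on a non-primary objective.

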### Inclusion criteria

Histopathology-proven MIBC on TURb or ≥ T3 on conventional imaging treated with MIBC radical treatmentT1–4 N0–3 M0 MIBC on conventional imaging (thoracic CT and abdominopelvic CT/ MRI)Age > 18 yearsWHO 0–2Willingness to undergo ^18^F-FDG-PET-CTWillingness to undergo MDT or immunotherapy, in case of diagnosis of oligometastatic or polymetastatic disease on ^18^F-FDG-PET-CT, respectivelyWillingness and ability to provide a signed informed consent according to ICH/GCP and national/local regulations

### Exclusion criteria

Presence of distant metastasis on conventional imaging (thoracic CT and abdominopelvic CT/ MRI)Refusal of or having contraindications to ^18^F-FDG-PET-CTRefusal of MDT or immunotherapyPrior radiotherapy unabling MDTContraindications to radiotherapy (including active inflammatory bowel disease)Contraindications to immunotherapyOther primary tumor diagnosed < 5 years ago and for which treatment is still required, except for diagnosis of non-metastatic prostate cancer at time of diagnosis of MIBC or non-melanoma skin cancer.

### Evaluation and inclusion

Patients who were recently diagnosed with MIBC on TURb and who are considered for curative treatment, will be informed of this clinical study if eligible at the departments of urology, radiation oncology, medical oncology or at the multidisciplinary consultations as carried out in some participating centers. The decision to participate will be entirely voluntary. Eligible patients who decide not to participate will be offered standard of care treatment.

### Intervention

#### Imaging

Conventional imaging, consisting of standard thoracic CT and abdominopelvic CT (or MRI), will be performed prior to the radical local therapy. In case of neo-adjuvant chemotherapy, conventional imaging will be performed prior to and after neo-adjuvant chemotherapy. After the second cycle of chemotherapy, MRI bladder will be performed to evaluate provisional therapy response. In addition to and at timing of the conventional imaging patients will receive an ^18^F-FDG-PET-CT. We aim to perform the ^18^F-FDG-PET-CT within 1 month of the thoracic CT and abdominopelvic CT (or MRI).

The ^18^F-FDG-PET-CT procedure is described in detail in an additional file (see Additional file 2).

Conventional imaging images will be evaluated by experienced radiologists in uro-oncology. ^18^F-FDG-PET-CT images will be reviewed and analyzed by a nuclear medicine physician and a radiologist experienced in reading PET-CT images. Evaluation of the ^18^F-FDG-PET-CT images will occur blinded to the conventional imaging or vice versa in case the ^18^F-FDG-PET-CT is performed first.

After ruling out presence of distant metastases on conventional imaging and evaluation of the ^18^F-FDG-PET-CT’s, patients will be allocated to the appropriate treatment arm:
Arm 1: ^18^F-FDG-PET-CT ➜ T1–4 N0–3 M0Arm 2: ^18^F-FDG-PET-CT ➜ T1–4 N0–3 M1 (≤3 metastases)Arm 3: ^18^F-FDG-PET-CT ➜ T1–4 N0–3 M1 (> 3 metastases)

If no neo-adjuvant chemotherapy is administered, group allocation is based on the findings of the single ^18^F-FDG-PET-CT. In case of neo-adjuvant chemotherapy, group allocation is based on ^18^F-FDG-PET-CT with the highest number of distant metastases. Thus, patients who show a decrease of the total number of metastases or a complete response on the second ^18^F-FDG-PET-CT, will be allocated based on the result of their first ^18^F-FDG-PET-CT.

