**Fig. 1 Fig1:**
[figure not shown]
Overview of the EFFORT-MIBC study design. (1) Inclusion and exclusion criteria need to be fulfilled to be included in the study. (2) Stratification into treatment arms is based on the ^18^F-FDG-PET-CT result. In case of neo-adjuvant chemotherapy, stratification is based on the results of both ^18^F-FDG-PET-CT’s (e.g. prior to and after neo-adjuvant chemotherapy). Abbreviations: MIBC: muscle-invasive bladder cancer; CT: computed tomography; MRI: magnetic resonance imaging; ^18^F-FDG-PET-CT: ^18^F-fluorodeoxyglucose-positron emission tomography-computed tomography; MDT: metastasis-directed therapy

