#### Subsequent analyses

Descriptive statistics will be used to summarize patient characteristics and toxicity per treatment group. Progression and survival are defined as mentioned above and calculated from time of diagnosis to disease progression or death. Survival analysis will be compared between groups using the log-rank test. Kaplan-Meier estimates of 2-year PFS, DMFS, DSS and OS will be provided for each treatment group and as a post-hoc subgroup analysis based on patient characteristics described above. Median follow-up time will be derived using both complete and incomplete follow-up times. Cox proportional hazards regression will be used to provide hazard ratio estimates. A *p*-value of less than 0.05 will be considered statistically significant. For the evaluation of biomarkers on one time point, differences between groups will be tested using the Mann-Whitney U test. For the evaluation of biomarkers over time, differences between groups will be tested using the Wilcoxon signed-rank test. To evaluate correlations, Spearman correlation coefficients will be calculated. A p-value of less than 0.05 will be considered statistically significant.

All statistical analyses will be performed using SPSS (SPSS Inc., Chicago, Il, USA).

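### Arms set by a PET after chemotherapy, with survival counted from diagnosis, give patients upstaged at that PET immortal time in arms 2/3; the effect on the test against 38% is probably small

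*Protocol article*

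**What the plan says.** **How the arm is set.** Under Imaging, the protocol article assigns patients without chemotherapy by their single PET. For those with neo-adjuvant chemotherapy, "conventional imaging will be performed prior to and after neo-adjuvant chemotherapy", and PET is tied to each of these rounds: "In addition to and at timing of the conventional imaging patients will receive an" FDG-PET-CT. Allocation then follows the PET "with the highest number of distant metastases". The Fig. 1 legend agrees: "In case of neo-adjuvant chemotherapy, stratification is based on the results of both" scans. The text spells out only the patient whose count falls or who responds completely, and who keeps the arm of the first PET. The rule also works the other way: a higher count on the second PET decides the arm.

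**Where time starts.** Under Objectives, the primary endpoint is the 2-year survival rate, "defined as the percentage of patients alive at 2 years after diagnosis of MIBC", and "OS is calculated from time of diagnosis until death due to MIBC or other causes". The three secondary time-to-event endpoints are also defined from diagnosis. Subsequent analyses repeats that progression and survival are "calculated from time of diagnosis to disease progression or death".

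**How arms are analysed.** Kaplan-Meier estimates are given per treatment group, and "Survival analysis will be compared between groups using the log-rank test". Cox regression supplies hazard ratios. Sample size tests the 2-year survival of arms 2+3 against 38% with an exact binomial test.

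The article mentions no landmark, delayed entry or time-dependent arm. It also does not say where a patient who dies before the second PET is counted.

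**The concern.** Group membership depends on a result obtained after the clock has started. A patient who is M0 on the first PET and M1 on the second joins arm 2 or 3 only by living to the second PET, yet the time before that scan is credited to arm 2 or 3. No death can occur in that arm during this stretch. A patient on the same course who dies during chemotherapy can never enter arms 2+3. The same applies between arms 2 and 3 when the count rises from at most three to more than three metastases.

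The results at stake are every by-arm curve, the log-rank tests and the hazard ratios. For the pooled arms 2+3 test against 38%, only M0-to-M1 converters matter. Patients who are M1 on the first PET and keep their arm carry no such time up to the second scan, and patients without chemotherapy have no second scan. Chemotherapy patients also have two chances to be PET-positive, and the others have one.

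**Working it through.** **1. The plan's own figure.** Inputs from Sample size: null 38%, alternative 63%, n = 35, alpha 5%, 10% drop-out, one quarter PET-positive. Sidedness is not stated.
- Two-sided 5% (upper tail at most 0.025): reject at 20 or more survivors of 35. P(X ≥ 20 | 35, 0.38) = 0.0167; power P(X ≥ 20 | 35, 0.63) = 0.815.
- One-sided 5%: reject at 19 or more; error 0.0367, power 0.892.
- The two-sided reading fits the stated 80%. 35/0.90 rounds up to 39, and 39/0.25 = 156.

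The design reproduces, and the point made here does not change its arithmetic.

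**2. Model for the shift.** Let *f* be the share of arms 2+3 classified only at the second PET, and *m* the probability of dying before that PET. With no treatment benefit, a converter's 2-year survival given survival to the second PET is 0.38/(1 − m). The pooled null rate is

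p = (1 − f) × 0.38 + f × 0.38/(1 − m),

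and the error is P(X ≥ 20 | 35, p). The documents give neither *f* nor *m*, and no date for the second PET. Assumed: f = 25–50%, second PET at 3–4 months, exponential survival.

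**3. Choice of m.** Converters were PET-negative at the first scan, so a PET-negative hazard is the more natural one before the second scan. The Background reports a 35-point gap in 2-year survival in favour of PET-negative patients. If 38% is the PET-positive rate, the PET-negative rate is about 38 + 35 = 73% (an inference). Then m = 1 − 0.73^(3/24) = 3.9% at 3 months and 1 − 0.73^(4/24) = 5.1% at 4 months. As a high case, the PET-positive hazard gives m = 1 − 0.38^(3/24) = 11.4% and 1 − 0.38^(4/24) = 14.9%.

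**4. Results** (cut-off 20/35; reference 38.0% and 0.0167).

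| Mortality before second PET | f | Pooled null 2-year OS | Upper-tail error |
|---|---|---|---|
| 3.9% (3 months) | 25% | 38.4% | 0.019 |
| 5.1% (4 months) | 50% | 39.0% | 0.023 |
| 11.4% (3 months) | 25% | 39.2% | 0.024 |
| 14.9% (4 months) | 50% | 41.3% | 0.043 |

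Example, second row: 0.5 × 0.38 + 0.5 × 0.38/0.949 = 0.190 + 0.200 = 0.390.

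With m of 1–5% and f of 10–50%, the pooled null is 38.0–39.0% and the error 0.017–0.023.

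**5. Between arms.** The direction depends on a rule the article does not give.
- If deaths before the second PET are counted in arm 1, arm 1 takes all early deaths of would-be converters and the contrast between arms is most distorted.
- If such patients stay unallocated, chemotherapy patients in arm 1 also have guaranteed time up to the second PET, and the contrast shrinks. The 2-year rate of arms 2+3 still carries the converters' guaranteed time.

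**The case against.** Several counter-arguments have weight.

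- **Small early mortality.** Patients are WHO 0–2 and considered for curative treatment, and converters received chemotherapy. Under Treatment, a patient with metastases on conventional imaging before local treatment starts is excluded, so a converter must be newly PET-positive and still negative on CT/MRI. This makes a high early death rate implausible and a large converter share doubtful. It stands, and it is why the 4–5% case is the main one.
- **Offsetting prognosis.** Converters developed PET-visible metastases despite chemotherapy. The working gives them the same hazard after the second PET as the rest of arms 2+3. A worse one could cancel the gain. This also stands.
- **The arms are not randomised.** They differ in prognosis by construction, so a shift of a point or so is minor beside that difference. True, but it does not justify adding an avoidable bias.
- **A SAP might contain a landmark.** It might. The article nevertheless fixes the allocation rule and the time origin together, and these two produce the problem.

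A reader might infer that survival is necessarily biased downward in arm 1, because deaths before the second PET stay there. The article does not say so; its wording on allocation after evaluation of the scans is equally compatible with such patients being unallocated. A reader might also infer that the primary test is materially pushed toward success. That needs the high mortality case and a large converter share, and the documents support neither.

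**Conclusion.** The point holds as a time-origin problem. Patients upstaged at the second PET carry guaranteed survival time in arm 2 or 3, and this biases the by-arm Kaplan-Meier, log-rank and Cox results as planned.

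For arms 2+3 against 38%, the effect is probably small: a null rate of about 38.4–39.0% and an upper-tail error of 1.9–2.3% instead of 1.7%, which stays under the 2.5% upper tail. With 11–15% early mortality it would be 39.2–41.3% and 2.4–4.3%. These ranges rest on an assumed converter share of 25–50%, a second PET at 3–4 months, exponential survival, the two-sided reading of alpha, and equal prognosis after the second PET. None of the first three is in the article. The net effect on the test cannot be settled from the document, and neither can the time origin behind the 38% benchmark.

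**What to change.** Leave treatment allocation unchanged and alter only the analysis.

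1. State where patients who die or drop out before the second PET are counted.
2. In the by-arm Kaplan-Meier, log-rank and Cox analyses, use delayed entry or a landmark at the allocating PET, or treat arm as time-dependent in Cox. Apply this to all arms, including chemotherapy patients in arm 1, whose status is complete only after the second PET.
3. For the arms 2+3 binomial test, keep diagnosis as the origin, since delayed entry does not fit a test of the percentage alive 2 years after diagnosis. Add an analysis with arms set by the first PET only, and show second-PET converters separately. If the origin is moved, define the 38% benchmark from the same point; n = 35/39/156 then stays as it is.

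Cost: the PET dates must be captured, which the article does not confirm. Some early person-time is lost, and delayed entry may need software other than the named SPSS. The first-PET analysis needs no special software.
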